#### Surgical complications

Postoperative complications, divided into systemic and local, are evaluated over the 8 weeks of postoperative follow-up, and their percentages are compared between the study and control groups. The following complications are considered systemic: the need for hospital readmission, postoperative blood loss with an indication for blood transfusion, deep vein thrombosis (diagnosed by ultrasound examination), pulmonary embolism (diagnosed using an angiographic examination) and death.

The following complications are considered local: seroma (accumulation of serous subcutaneous fluid evident upon physical examination after removing the drain and following at least one aspiration); haematoma (accumulation of haematic subcutaneous fluid evident upon physical examination after removing the drain and following at least one aspiration); wound infection (based on the definition established by the Centers for Disease Control and Prevention (CDC) [55]); wound dehiscence (defined as separation of the wound margins requiring medical or surgical treatment [56]); and necrosis (defined by the presence of devitalised tissue that extends through the full thickness of the skin, requiring surgical debridement).

#### Dietary survey

To determine whether there are differences in the iron dietary intake levels between the two groups, a dietary survey is conducted. At the eighth postoperative week, patients answer a 24-hour diet recall survey in which they report all food and drinks consumed during the previous day, from breakfast to dinner [57]. The recall is administered by a professional dietician following the recommendations of the Nordic Cooperation Group of Dietary Researchers [58]. NutWin version 3.0 software, developed and validated by the Federal University of São Paulo (Universidade Federal de São Paulo), is used to calculate dietary iron intake [59].

#### Menstruation

Because prolonged menstrual bleeding lasting more than 7 days can have an impact on Hb levels [60], all patients are asked during the follow-up period whether they have had menstrual bleeding lasting for more than 7 days.

### Sample size

A sample size of 56 patients (28 per group) was calculated, assuming an 80 % statistical power to detect a minimum difference in Hb levels of 1.5 g/dL (the primary outcome), considering a standard deviation for Hb levels of 1.84 [61], a two-tailed significance level of 0.05 and a patient loss to follow-up of 10 %.

The need for postoperative follow-up assessments of participants, the relatively brief 8-week follow-up period, the flexibility to decrease the iron oral dose to one tablet daily for patients reporting gastrointestinal symptoms, and reminder sessions for treatment adherence might reduce participant attrition and, consequently, the attrition bias.

### Recruitment

Patients are recruited from the post-bariatric plastic surgery outpatient clinics of Hospital do Servidor Estadual and Hospital São Paulo via local advertisements. Patients on hospital waiting lists are also identified. Both hospitals have active bariatric surgery services that regularly refer patients to the post-bariatric plastic surgery outpatient clinic; therefore, we do not expect challenges regarding patient recruitment.

### Methods – assignment of interventions

#### Allocation – sequence generation

The patients are allocated to the study or control group at a ratio of 1:1 using a computer-generated randomiser (http://www.randomization.com) with fixed block sizes. The block sizes are kept confidential.

#### Allocation – concealment mechanism

Opaque, sealed, serially numbered envelopes containing carbon paper and aluminium foil inside are used to maintain the confidentiality of the random allocation. The researchers responsible for the recruitment do not receive any information regarding the groups into which the patients are allocated. The allocation of the study participants was defined using a computer-generated random sequence. Confidentiality of the block size and blinding patient allocation using a series of opaque, sealed, and numbered envelopes were used to reduce selection bias.

#### Allocation: implementation

A surgical team member who did not participate in the recruitment of patients generated the allocation sequence and maintained the allocation concealment. The researchers responsible for recruitment did not receive any information regarding the patient allocation groups. The sequentially numbered envelopes remained stored with the surgical team member throughout the study. Prior to the post-bariatric abdominoplasty surgery, the surgeon wrote the name of the patient on the envelope that corresponded to the numerical sequence of the research. At the end of the surgery, the envelope was opened, revealing the research group to which the patient belonged.

### Blinding

Due to the nature of the intervention (orally administered iron supplements result in blackening of the stool [62], facilitating the identification of the allocation group), we chose not to blind the patients or researchers to the allocation group. However, the surgeon who evaluates the incidence of local complications is blinded to the allocation group. In addition, the patients are not informed about the outcome of their laboratory tests to prevent the knowledge of their test results from influencing their responses on the quality of life questionnaires [63]. The use of an objective laboratory measurement as the primary endpoint (Hb level) also reduces detection bias.

Although unmasked clinical trials are subject to performance bias, the disclosure of allocation concealment at the end of the surgery reduces the possibility of surgical team performance bias during surgery. In addition, both the recommendation to use the same vitamin and mineral supplementation and the written supply of the same nutritional guidelines for all participants aim to reduce performance bias over the postoperative follow-up period.

### Methods – data collection, management, and analysis

#### Data collection methods

Researchers collect patient demographic data using a standardised form for all study patients.

#### Data collection methods – retention

The night before each outpatient visit, patients are contacted by telephone and reminded of the importance of collecting blood for laboratory tests, completing the quality of life questionnaires, and the medical evaluation.

#### Data management

All data collected during the study are entered into two separate spreadsheets at different times. The two spreadsheets are then compared with each other to ensure the accuracy of the data collected [64].

### Statistical methods

#### Statistical methods – outcomes

The data will be entered into the statistical software Statistical Package for the Social Sciences (SPSS), version 17.0, and initially evaluated descriptively using summary measures (means, standard deviations, minima, maxima, and quartiles). To guarantee reliability and avoid selective outcome reporting, a fully specified statistical analysis plan will be written before unmasking.

To analyse the behaviour of variables for quality of life, Hb level, reticulocyte count, iron profile and CRP level at different times, a repeated measure analysis of variance (ANOVA) will be employed. This model will presuppose the normality of the data tested in the residuals (difference between the observed and estimated value) of the fitted model using the Kolmogorov-Smirnov test.

To determine the presence of an interaction between group and time, the means of the variables between groups will be compared at each time-point using Student’s *t* test for independent samples, and means between different time-points for each group will be compared using Student’s *t* test for paired samples.

For those variables in which there is a lack of normality in the data, non-parametric Mann-Whitney tests will be performed to compare the differences between groups at each time-point, and the Wilcoxon test will be used to compare patterns over time for each group. Bonferroni correction will be used for these tests to ensure an overall significance level of 5 %.

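### The 80% power assumes a single week-8 haemoglobin test at an uncorrected two-sided 0.05, and the analysis section does not secure that test

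*Protocol article*

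**What the plan says.** **Sizing.** Protocol article, *Sample size*: "A sample size of 56 patients (28 per group) was calculated" for 80% power to detect 1.5 g/dL, "considering a standard deviation for Hb levels of 1.84" g/dL and with "a two-tailed significance level of 0.05 and a patient loss to follow-up of" 10%. No multiplicity adjustment is mentioned.

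**Analysis.** *Statistical methods – outcomes* lists Hb with quality of life, reticulocytes, iron profile and CRP. All go into a repeated-measures ANOVA whose residuals are checked with a Kolmogorov-Smirnov test. The groups are then compared by t test at each time-point, with paired t tests within groups. In a separate paragraph, for variables lacking normality, "non-parametric Mann-Whitney tests will be performed to compare the differences between groups at each time-point" and Wilcoxon tests are used within groups. That paragraph closes: "Bonferroni correction will be used for these tests to ensure an overall significance level of" 5%.

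**Primary outcome.** *Primary outcome measures* defines it as a difference in mean Hb at week 8, and the *Discussion* names week 8 as the primary time-point. *Adjusted analyses*, placed under additional analyses, gives week-8 Hb an ANCOVA on baseline Hb, ferritin and transferrin saturation, with no correction attached. It says adjusted and unadjusted results will both be reported.

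**The concern.** A confirmatory test needs one alpha, one test statistic and one target quantity, all fixed in advance and matching the sample-size calculation. The sizing section supplies these, but the analysis section does not carry them through. Hb goes through the general scheme, and nothing says that the week-8 comparison stands outside the correction.

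The open phrase is *these tests*. It may mean only the rank tests of its own paragraph, or all the pairwise tests described in the section. Under the wide reading the primary test is run at a smaller alpha than the trial was sized for. Under the narrow reading a pretest chooses both the alpha and whether means or ranks are compared. That pretest uses residuals of the whole repeated-measures model, so Hb values from other visits can change how week 8 is tested.

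At stake is the trial's main conclusion. A week-8 p-value of 0.03 would be positive at 0.05 and negative at 0.05/3 or 0.05/4.

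**Working it through.** **Inputs (*Sample size*).** Difference 1.5 g/dL; SD 1.84 g/dL; two-sided alpha 0.05; power 80%; loss 10%; allocation 1:1. Hb is measured preoperatively and at weeks 1, 4 and 8 (*Laboratory variables*).

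**Step 1: reproduce the stated size.** The standardised difference is 1.5/1.84 = 0.815.
- Normal approximation: n = 2(1.960 + 0.842)²/0.815² ≈ 23.6, so 24 per group; 24/0.9 = 26.7, so 27 per group and 54 in total.
- Noncentral t, with df = 2n − 2 and noncentrality 0.815 × √(n/2): n = 25 is the smallest size reaching 80%, with power 80.6%. Then 25/0.9 = 27.8, so 28 per group and 56 in total.

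The t-test calculation matches the article exactly. The sizing is therefore for one unadjusted test, with no reserve for a correction.

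**Step 2: power if Bonferroni covers the week-8 test.** The same noncentral t calculation is used with alpha = 0.05/k. The article gives no k, so three values are assumed: 3 (weeks 1, 4 and 8), 4 (adding the preoperative comparison) and 16 (4 between-group tests plus 6 paired comparisons in each of 2 groups).

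| k | alpha | power, 25 per group | power, 28 per group (no loss) | total N for 80% with 10% loss |
|---|---|---|---|---|
| 1 | 0.05 | 80.6% | 85.0% | 56 |
| 3 | 0.0167 | 65.6% | 71.7% | 74 (33/0.9, so 37 per group) |
| 4 | 0.0125 | 61.4% | 67.9% | 80 (36/0.9 = 40 per group) |
| 16 | 0.0031 | 41.9% | 48.9% | 104 (46/0.9, so 52 per group) |

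The loss is 80.6 − 65.6 = 15.0 points for k = 3 and 80.6 − 61.4 = 19.2 points for k = 4.

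**Step 3: power if Bonferroni covers only the rank tests.**
- Normality not rejected: t test at 0.05, power 80.6%.
- Normality rejected: Mann-Whitney at a corrected alpha. Simulation with 25 per group and normal data gives 62.8% (k = 3) and 58.7% (k = 4). These are indicative only, since this branch is entered when the data do not look normal.
- The switch to ranks alone costs little: Mann-Whitney at 0.05 has 78.2% by simulation, or about 80% using the relative efficiency of 0.955 under normality.

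The loss therefore comes from the Bonferroni factor. The pretest matters because it decides whether that factor applies, and because a rank test does not estimate the mean difference that defines the primary outcome.

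**Step 4: the ANCOVA.** At 0.05 it would keep about 80% or more. At a corrected alpha, a multiple correlation of about 0.5 (k = 3) or 0.55 (k = 4) between the covariates and week-8 Hb would roughly restore 80%. The article gives no such correlation, so this is an assumption.

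**The case against.** A reader might infer that the trial is underpowered, or that either the 80% power or the 5% error rate must be false. The document supports neither.

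- **Wording.** The Bonferroni sentence ends the paragraph on non-normal variables, directly after the rank tests, which are its most natural antecedent. The t tests sit in a paragraph with no correction. On that reading, with normality not rejected, week-8 Hb is tested at 0.05 and both the power and the 5% error for the primary claim hold. This stands, so the power loss is conditional.
- **One primary time-point.** The *Discussion* names week 8. A family error of about 13–18% for four uncorrected t tests (simulated, within-patient correlation 0.7 to 0.3) would treat all four visits as equal routes to a positive trial, which they are not. This stands too.
- **A separate ANCOVA.** It carries no correction and could deliver the planned power. But it is listed as an additional analysis and is not named as decisive, and the unadjusted result to be reported beside it has no source other than the general scheme. It adds a second candidate for the primary test.
- **Left to the analysis plan.** The article promises a fully specified plan before unmasking, and defining a multiplicity family is commonly left to such a plan. The lack of a list of tests is therefore no fault in itself. The point is that the stated rule can send the primary outcome to an alpha, or to a rank test, that the sizing does not allow for; a plan that follows the article inherits this. In a trial where neither patients nor researchers are blinded, that deadline also marks no clear date.

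**Conclusion.** The concern holds in conditional form. The sample size is correct for one uncorrected two-sided 0.05 t test, and the analysis section does not guarantee that test.

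If the correction reaches week-8 Hb, power with 25 evaluable per group is about 66% (three tests) or 61% (four tests) before any gain from covariates. The 42% figure needs all 16 between-group and paired tests in one family and is an outer bound among the cases examined. If the correction is confined to the rank tests, 80% is kept when normality is not rejected, but the alpha and the target of the primary test rest on a pretest. The family sizes are assumptions throughout. That 80% power has been lost is not shown; that it is not secured is.

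**What to change.** - Name one mean-based analysis of week-8 Hb as the single confirmatory test, at two-sided 0.05, whatever the Kolmogorov-Smirnov result and outside any Bonferroni family. The ANCOVA already planned is a natural choice; the unadjusted comparison is then supportive.
- Apply Bonferroni or Holm only to Hb at weeks 1 and 4 and to the secondary variables, whichever test is used, and list the tests covered.
- Drop the preoperative between-group significance test. Allocation is revealed at the end of surgery, so any preoperative difference is due to chance, and testing it could only enlarge the family.
- If the primary test is meant to be corrected, say so and restate its power at the corrected alpha: about 61–66% for four to three tests, before covariate adjustment.

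This costs a few sentences in the protocol and analysis plan, with no new patients or data. The only downside is a stricter threshold for secondary t tests. It should be dated before any comparison by group; the article reports 19 patients operated on by August 2015.

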### Statistical methods: additional analyses

#### Adjusted analyses

The final mean Hb levels in the eighth postoperative week (primary outcome) will be adjusted for baseline Hb level, ferritin levels, and TSI via an analysis of covariance (ANCOVA). Both the adjusted and unadjusted analyses will be reported in the final publication.

### Statistical methods – analysis population and missing data

Data analysis will be performed based on the original allocation of all patients as defined by randomisation, regardless of the degree of adherence to the protocol (intention-to-treat principle).

With respect to missing data, the amount thereof, their patterns and variables associated with omission will define the most appropriate technique to be used in the processing of such data, whether in the primary analysis or the sensitivity analysis. For primary analyses, methods will be used that make use of all available data, such as multiple imputations. To reduce the presence of incomplete data and attrition bias, the need to discontinue the allocated treatment will be considered as treatment failure.

### Dissemination

#### Protocol amendments

Any changes to the protocol that might affect the study, the potential benefits for patients, or their safety (including changes to the study objectives, design, patient population, sample size, study procedures, or significant administrative aspects) will require a formal amendment to the protocol. These changes will be agreed upon among the researchers and will require approval from the Research Ethics Committee before implementation.

### Confidentiality

All participant information will be kept in password-protected files, and the identifiable data will be replaced by codes.

### Access to data

All of the researchers involved in this study will have access to all of the collected data.

### Dissemination policy – authorship

The criteria for authorship of this protocol followed the guidelines established by the International Committee of Medical Journal Editors [65]. A team of professional translators was used to translate the text from Portuguese into English. The final report will follow the Consolidated Standards of Reporting Trials (CONSORT) 2010 guidelines.

## Discussion

Anaemia is the second most frequent complication following post-bariatric abdominoplasty [7]. Two months after surgery, these patients have still not recovered their preoperative Hb levels, and 45 % develop severe iron deficiency [13]. However, the recovery of Hb levels is considered an important factor in postoperative patient recovery [23]. This aspect becomes even more relevant in post-bariatric patients, as they often undergo a series of subsequent surgical procedures to treat deformities in different regions of the body; thus, they only have a short time to recover their haematological parameters [24].

A systematic review concluded that iron supplementation is effective in promoting an increase in Hb levels [37]. Although iron supplementation can be administered either orally or intravenously, it has been hypothesised that intravenous administration has improved efficacy in the population of post-bariatric patients given the difficulties with orally administered iron absorption in these patients [12]. This randomised clinical trial protocol was designed to test this hypothesis because no studies were found in the literature that evaluated the effect of iron supplementation in a population of patients undergoing post-bariatric surgery.

Blinding is commonly used in randomised clinical trials to reduce the risk of bias [66]. However, because orally administered iron supplementation can cause stool colour changes, the implementation of blinding in this study was considered to be impractical. In fact, most published randomised clinical trials evaluating the effect of iron supplementation in postpartum women were not blinded [67].

The primary outcome of this study is the detection of a minimum difference of 1.5 g/dL in the final mean values of Hb levels at the eighth postoperative week between the study and control groups. This difference in Hb levels was established based on the fact that the patients in the study group receive a total of 400 mg of intravenously administered iron, and 200 mg of iron is needed to increase Hb levels by approximately 1 g/dL [31]. This dose would be sufficient to recover the loss of approximately 2.1 g/dL of Hb that occurs during this type of surgery [13]. Because the control patients receive iron orally and the absorption of iron in these patients is compromised as a result of bariatric surgery [38], a difference in Hb levels of 1.5 g/dL between the study and control groups was considered to be biologically plausible.

The choice of a laboratory variable as a primary outcome rather than a more relevant clinical outcome, such as reduced blood transfusion rate or improved quality of life, could be considered a limitation of this study [68]. However, because each 1 g/dL increase in Hb increases the SF-36 vitality score from 1.2 to 7.4 points [69] and the minimum clinically relevant difference in the SF-36 vitality score is 5 points [70], a difference of 1.5 g/dL in Hb levels was considered to have the potential to be clinically relevant. Consequently, the response of Hb levels to treatment was defined as the primary outcome, as published in other protocols [71]. The eighth postoperative week was determined as the primary time-point for haemoglobinometric measurements because the postoperative recovery of Hb levels largely occurs between 4 and 6 weeks following major surgery [72, 73].

It is unlikely that the use of intravenously administered iron compared to orally administered iron can significantly alter relevant clinical outcomes, such as hospital readmission or mortality rates. However, there is an increasing recognition of the importance of the benefits of small interventions in surgical care as opposed to a single ‘magical’ intervention to improve outcomes following surgery [74]. Furthermore, iron supplementation runs counter to a paradigm shift known as patient blood management.

Patient blood management has been increasingly accepted as an effective means of reducing blood transfusion rates and improving postoperative outcomes [75]. It is defined as the application of evidence-based medical and surgical concepts aimed at superior clinical outcomes through the improved utilisation of the patient’s own blood instead of donor blood. Such management is intended to maintain the concentration of Hb, to optimise homeostasis and to minimise blood loss. It consists of three pillars: (1) optimising erythropoiesis, (2) minimising blood loss, and (3) promoting a greater tolerance to anaemia [76]. Intravenously administered iron supplementation falls under the first pillar. The proposed study represents a randomised clinical trial designed to assess the effect of intravenously administered iron supplementation in treating anaemia following post-bariatric abdominoplasty.

### Trial status

Recruiting. The first patient was randomised in April 2014; by August 2015, 19 patients had undergone surgery.

## Abbreviations

FACIT-F: Functional Assessment of Chronic Illness Therapy – Fatigue
BMI: body mass index
Hb: haemoglobin
TSI: transferrin saturation index
CRP: C-reactive protein
SF-36: Short-Form 36 Health Survey
CTAE: Common Terminology Criteria for Adverse Events
CDC: Centers for Disease Control
USA: United States of America
CAAE: Certificado de Apresentação para Apreciação Ética (Presentation Certificate for Ethical Assessment)
